### Statistical analyses

2.8

Kolmogorov–Smirnov tests will assess normality, and the appropriate repeated measures test employed (e.g., repeated measure ANOVA or Friedmann’s test) to compare glucose outcomes by treatment condition. The primary analysis will be intention to treat; per protocol associations will also be explored. Linear mixed-effects models (i.e., PROC MIXED in SAS) will allow for comparisons of the glucose outcomes across the three treatment conditions with adjustment for GGI or GDM status, BMI, and diet (that is, HEI (53) and/or grams of carbohydrate). Linear mixed-effects models will be additionally adjusted for the volume of PA from activities of daily living during waking hours (or background PA). Modified PSQI (sleep) metrics will also be compared across the three conditions using linear mixed-effects models adjust for GGI or GDM status, sleep duration, number of waking episodes, and PA. Mood states will be compared between the early PA and late PA conditions only, potentially controlling for PA modality (e.g., walking, stepping, or both), circumstances (e.g., while listening to music), and/or intensity (e.g., volume of PA in MET minutes). If needed, multiple imputations will be used to handle missing data.

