### Consent and randomization

2.3

Potential participants are invited to schedule an Information Session (remote or in-person) to learn more about the study. They are emailed a link to the study consent form and asked to review it ahead of the Information Session. The consent and all study procedures are reviewed at the Information Session; time is allotted to answer questions prior to signing the consent.

Participants are then randomized in SAS to either morning PA followed by evening PA or evening PA followed by morning PA (**Figure 1**, [*18*]); the crossover design allows each participant to serve as their own control. Participants are instructed to perform no PA for health or wellness on the day of the Study Visit (i.e., day 0) and on days 2, 5, and 7, which served as wash-out days. PA (described in greater detail in the following section) is performed on days 3 and 4 and again on days 8 and 9. No PA for health or wellness is performed on days 1 and 6, thereby providing two full days’ (i.e., 48 h) worth of data under each treatment condition (i.e., morning PA, evening PA, and no PA).

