#### Device data processing and cleaning

2.5.2

Physical activity and sleep are assessed using ActiGraph’s (now Ametris’) CentrePoint Insight Watch. The Watch data are downloaded from ActiGraph’s (now Ametris) CentrePoint system, a cloud-based platform designed to manage and analyze physical activity and sleep data. The de-identified raw (32 Hz sampling rate) device data are exported as 1-second epochs and raw CSV files and read into RStudio. The device sensor data are first examined for wake and sleep times. Sleep time and non-sleep time are defined using participant sleep diaries. Next, the non-wear time is identified using the Choi algorithm (36–38). Days with less than 600 min of non-sleeping wear time will be excluded from the analyses.

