Potential limitations include the possibility that a participant is put on glucose-lowering medication or delivers their neonate during the study period, which would limit and potentially introduce an imbalance in the number of observation days available for analyses per treatment condition. Poor adherence to PA, that is, its prescribed timing, duration, and intensity, could also limit the trial’s findings. Therefore, we carefully vet potential participants at the Information Visits, emphasize the importance of PA, develop a PA Action Plan at the Study Visit, and offer text message reminders for their PA on the days/times it is assigned. Finally, the two-regression algorithms were validated among healthy non-pregnant adults; thus, it is possible that it underestimates PA intensity (METs) in pregnant individuals or late in pregnancy, which could result in a Type 2 error in per-protocol analyses.

This crossover trial will provide valuable insights into whether the timing of postprandial PA, that is, in the morning following breakfast vs. the evening following dinner, differentially impacts glucose levels in individuals with pregnancy hyperglycemia. This investigation will also be the first to provide comprehensive data on the composition and distribution of dietary intake, and sleep in individuals with pregnancy hyperglycemia. We hope that the Time to Move Randomized Crossover Trial will motivate future studies to integrate serial measurements of health behaviors with CGM data and that our findings will lead to a more specific, that is, time of day-based, recommendation for PA in individuals with pregnancy hyperglycemia.

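### No listed analysis of this order-randomised crossover includes period, the test is picked by a normality pretest, and the fate of incomplete participants is left open

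*Protocol article*

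**What the plan says.** Section 2.3 (Consent and randomization) describes the allocation: "Participants are then randomized in SAS to either morning PA followed by evening PA or evening PA followed by morning PA". Activity falls on days 3 and 4 and again on days 8 and 9. The no-activity days are 1 and 6 in both sequences. Allocation uses blocks of 4, stratified by GGI and GDM.

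Section 2.8 (Statistical analyses) sets out two kinds of analysis for glucose.

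- First, "Kolmogorov–Smirnov tests will assess normality, and the appropriate repeated measures test employed" (repeated-measures ANOVA and Friedman are the examples given) "to compare glucose outcomes by treatment condition".
- Second, "Linear mixed-effects models (i.e., PROC MIXED in SAS) will allow for comparisons of the glucose outcomes across the three treatment conditions". The covariates named for these models are the stratum (GGI or GDM), BMI, diet and background activity.

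The same section states: "The primary analysis will be intention to treat; per protocol associations will also be explored". It allows multiple imputation where needed, without saying when that is. It does not say whether the ANOVA/Friedman step or the mixed model carries the primary comparison.

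Section 2.7 sizes the trial on a repeated-measures ANOVA: power 0.89 with 36 participants at a significance level of .007. It raises the target to 39 because a participant could start insulin or deliver during observation. The Discussion adds that such events could "introduce an imbalance in the number of observation days available for analyses per treatment condition".

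**The concern.** There are three linked weaknesses.

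**Period.** The randomised factor is the order of two activity blocks five days apart. Any drift between the blocks, from whatever cause, enters each participant's morning-minus-evening difference with opposite sign in the two sequences. Without a period term that drift becomes residual variance. If the sequences are unequal, part of it also enters the estimate. Neither the ANOVA/Friedman step nor the printed covariate list contains period.

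**Incomplete participants.** Standard repeated-measures ANOVA and Friedman need a value in every condition. A participant who starts insulin or delivers after day 4 has a no-activity day and a full activity block, yet would contribute nothing to such a test unless the rest were imputed. That sits badly with an intention-to-treat aim.

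**Normality gate.** Letting a Kolmogorov–Smirnov result choose the test means that the trial data decide, outcome by outcome, whether means or ranks are compared, within one Bonferroni family of seven outcomes.

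**Working it through.** **Inputs.** From section 2.7: effect-variance ratio 0.15, correlation 0.15, f = 0.73, significance level .007, power 0.89 at N = 36, 39 randomised. From section 2.3: two sequences, blocks of 4, two strata. The period shift π (block 1 versus block 2) is not in the documents. It is assumed to be 0 to 0.75 single-condition SD.

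**1. The plan's own figure.** With three conditions, f = √(0.15 × 3 / (1 − 0.15)) = 0.728. The noncentrality is f² × 36 = 19.06 on 2 and 70 degrees of freedom. Power at .007 is 0.885 (0.887 with f rounded to 0.73). The stated 0.89 is reproduced, so the point does not rest on a wrong sample-size figure.

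**2. Cost of leaving out period, morning versus evening.** In single-condition SD units, the paired difference has variance 2 × (1 − 0.15) = 1.7. With equal sequences and no period term this becomes 1.7 + π². The inflation is 1 + π²/1.7 and the effective sample size is 36 divided by it. For power, the true morning–evening difference is set to 0.90 SD, which gives 0.89 at N = 36 and .007 when π = 0. Power and type I error come from 20,000 simulations with 18 participants per sequence.

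| Shift π (SD) | Inflation | Effective N of 36 | Power without period | Power with period | Type I error without period (nominal 0.05) |
|---|---|---|---|---|---|
| 0 | 1.000 | 36.0 | 0.89 | 0.89 | 0.050 |
| 0.25 | 1.037 | 34.7 | 0.88 | 0.89 | 0.046 |
| 0.5 | 1.147 | 31.4 | 0.85 | 0.89 | 0.037 |
| 0.75 | 1.331 | 27.0 | 0.79 | 0.89 | 0.022 |

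The omission is therefore conservative: the test rejects too rarely, not too often.

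**3. Bias.** Bias in morning minus evening = (difference in sequence sizes / N) × π. With 39 participants in two strata and blocks of 4, the difference can only be 1 or 3.

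- 20 v 19 gives 1/39 = 2.6% of the shift.
- 21 v 18 gives 3/39 = 7.7%. It needs an unfinished half-block in one stratum to hold two of the same sequence (probability 1/3) and to lean the same way as the odd stratum (1/2), so its probability is at most 1/6.
- After uneven attrition to 20 v 16, the figure would be 4/36 = 11%.

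**4. Complete-case loss, if it happened.** ANOVA power at .007 by number of complete participants is 0.916 (39), 0.885 (36), 0.844 (33) and 0.792 (30). Losing the three spare participants (3/39 = 7.7%) only returns the trial to its planned 36.

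**5. What a period term cannot do.** The no-activity days have mean day (1 + 6)/2 = 3.5 in both sequences. Each activity condition has mean day (3.5 + 8.5)/2 = 6 over the two sequences. Only morning versus evening is order-randomised.

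**The case against.** The strongest reply is that this is a condensed article and that design terms such as period are routine content of an analysis plan, which is not shown. That limits how firmly the omission can be read. It does not remove the point, because the article does print a covariate list, and it commits to choosing the test by a pretest.

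A reader might infer that incomplete participants are dropped and that the analysis is therefore not by intention to treat. The documents do not support this. Section 2.8 declares intention to treat, gives ANOVA and Friedman only as examples, plans mixed models that can use partial data, and permits imputation. What remains is a risk: the trial is sized on the ANOVA, no model is named as primary, and the imputation trigger is open. The listed mixed models do not close the gap as they stand, since they adjust for diet and background activity measured after randomisation and also lack period.

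A reader might also take "Days with less than 600 min of non-sleeping wear time will be excluded from the analyses" to remove valid CGM days. The sentence closes a section on processing the watch data, and CGM is described separately with no such rule. The natural reading is watch data only, so no criticism follows.

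It is also fair to say that no document supports a large period shift, that a small one costs little, and that with complete data a sequence term does not change the within-participant contrast. All of this stands. The term that matters is period.

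**Conclusion.** The point holds as one of precision and clarity, not of invalidity. For a trial that randomises order, no listed analysis includes period. The cost in power for morning versus evening is about 1 point at a shift of 0.25 SD, 4 at 0.5 SD and 10 at 0.75 SD, all on an assumed period effect and the plan's own correlation of 0.15. Bias is minor, typically 2.6% of the shift and at most 7.7% before attrition, and type I error is not inflated under equal sequences. Complete-case loss is possible under the text but is not what the text prescribes; its effect on power is small unless losses exceed the three allowed for. The normality gate is a separate avoidable weakness, because it leaves the hypothesis for each outcome to the data.

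**What to change.** Name one linear mixed model as primary for all continuous glucose outcomes:

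- fixed effects for condition, period (days 1–4 v 6–9), sequence and GGI/GDM stratum;
- a random participant effect, plus participant-by-condition for the paired days;
- all randomised participants with any CGM data.

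Replace the Kolmogorov–Smirnov gate with a transformation chosen in advance for skewed metrics, and keep Friedman as a sensitivity analysis. State when imputation applies.

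The cost is analysis wording and about two degrees of freedom. The investigators are to stay blinded until the results are drafted (section 2.3), so the change can be made before unblinding. The report should also say that comparisons with no activity are not order-randomised, since the period term cannot repair the fixed placement of days 1 and 6.

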This manuscript provides an overview of the Time to Move Randomized Crossover Trial. The Trial’s objective is to compare 30 min of moderate-intensity walking or stepping (30) (i.e., walking in place) under free living conditions, performed either in the morning (i.e., within 30 min to 40 min of starting breakfast) or in the evening (i.e., within 30 min to 40 min of starting after dinner). Previous research by our group suggests that stepping is an acceptable alternative to walking, and given the commonly cited barrier of a lack of time for PA, it may be advantageous in that it can be accomplished while performing other activities that are already part of the everyday routine (30). The primary outcomes include glucose metrics across the 24-hour cycle, assessed using continuous glucose monitors (CGM). We hypothesize that morning PA would improve daytime (6 a.m.–11:59 p.m.) glucose levels, as well as post-breakfast and post-lunch glucose levels, while evening PA will improve post-dinner, nighttime (12 a.m.–5:59 a.m.) (31), and pre-breakfast glucose levels, and thus ultimately improve 24-hour glucose levels. Secondary outcomes include mood during and sleep following bouts of PA. The timing of PA could potentially be leveraged to improve glucose management in this population, thereby leading to improved outcomes for mothers and children.

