Potentially eligible patients are identified by clinic and study staff, who review the electronic medical records to conduct a preliminary eligibility assessment. The study staff then briefly explain the study, either in-person (i.e., meeting the patient at their OGTT) or by phone or text message, to assess interest. Potentially eligible patients, per the preliminary assessment, are then reviewed by an MD for the final determination of eligibility.

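### PA-versus-no-PA contrasts are not randomised and carry part of any shared time trend (2.5 days' worth if linear), which no stated analysis adjusts for; morning versus evening is protected

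*Protocol article*

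**What the plan says.** Section 2.3 (Consent and randomization) states that participants are "randomized in SAS to either morning PA followed by evening PA or evening PA followed by morning PA". The position of the no-PA condition is not randomised: "No PA for health or wellness is performed on days 1 and 6", while PA "is performed on days 3 and 4 and again on days 8 and 9". The no-PA instruction also covers day 0 and applies "on days 2, 5, and 7, which served as wash-out days".

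Section 2.8 (Statistical analyses) first names a repeated-measures ANOVA or Friedman test of glucose by condition. It then names linear mixed models for "comparisons of the glucose outcomes across the three treatment conditions with adjustment for GGI or GDM status, BMI, and diet", with a further adjustment for background PA. For sleep, "Modified PSQI (sleep) metrics will also be compared across the three conditions using linear mixed-effects models", adjusted for GGI/GDM status, sleep duration, waking episodes and PA. None of these analyses lists study day, period or sequence.

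The Background hypothesises that morning PA improves some glucose windows, "while evening PA will improve post-dinner, nighttime" and other windows. It does not say what the improvement is measured against.

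**The concern.** Within each half of the schedule the no-PA day comes before both PA days, for everyone. Anything that moves glucose or sleep over the observation period for reasons other than PA is therefore partly confounded with PA versus no PA.

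The article gives grounds for expecting some movement in glucose. Recruitment can take place by "meeting the patient at their OGTT", close to the point at which diet counselling would start. Participants photograph what they eat. After the change of sensor described in section 2.5.1, they can see their own readings. The article names no comparable mechanism for sleep.

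The no-PA condition is one of the three levels in the planned test and in the power calculation. It is also a natural, though unstated, reference for a claim of improvement. A falling trend would make both timings look effective, and a rising one would hide a real benefit.

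**Working it through.** **1. The plan's own figure.** From section 2.7: variance ratio 0.15, correlation 0.15, three conditions, N = 36, alpha .007.
- f = sqrt(0.15 × 3 / (1 − 0.15)) = 0.728, stated as 0.73.
- Noncentral F with 2 and 70 df and noncentrality 36 × 0.73² = 19.2 gives power 0.888, stated as 0.89.

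The figure reproduces, and this point does not alter it.

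**2. Mean study day, from section 2.3.**
- No PA: (1 + 6)/2 = 3.5.
- Each PA timing, averaged over two balanced sequences: (3 + 4 + 8 + 9)/4 = 6.0.
- Gap: 2.5 days.

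**3. Bias under a shared linear drift of b per day** (participant effects, 18 per sequence).
- No time term: PA minus no PA is off by 6.0b − 3.5b = 2.5b for each timing. Morning versus evening is off by 0.
- Two-level period term: the gap is 3.5 − 1 = 2.5 in the first half and 8.5 − 6 = 2.5 in the second, so the bias stays at 2.5b.
- Linear study day: bias 0.

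From day 1 to day 9 is 8 days, so 2.5/8 = 31% of a linear change enters the contrast.

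**4. Effect on the three-condition test.** The documents give no drift, so a range is assumed, in SD of a two-day condition mean per day. Simulated null trials (N = 36, correlation 0.15, alpha .007) gave:

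| Drift (SD/day) | Day 1 to day 9 (8 × drift) | Bias (2.5 × drift) | Rejection rate |
|---|---|---|---|
| 0 | 0 | 0 | about 0.7% |
| 0.05 | 0.4 SD | 0.125 SD | about 1.5% |
| 0.10 | 0.8 SD | 0.25 SD | about 4.3% |

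For scale, if both timings had equal effects, the planned variance ratio would correspond to a PA-versus-no-PA difference of sqrt(0.15/(2/9)) = 0.82 SD.

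**5. Cost of a linear day term.** Within-condition day variation per participant is 2 × 2.5² for no PA plus 3² + 2² + 2² + 3² for PA, that is 12.5 + 26 = 38.5.
- One timing versus no PA: the SE is multiplied by sqrt(1 + 2.5²/38.5) = 1.08.
- Both timings pooled versus no PA: 0.1592/0.1443 = 1.10.
- Morning versus evening: unchanged.

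**6. Other drift shapes.** Size of bias in PA minus no PA for a change of 1 unit:

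| Shape | Unadjusted | With linear day |
|---|---|---|
| Exponential settling, time constant 3 days | 0.33 | 0.08 |
| Exponential settling, time constant 2 days | 0.38 | 0.14 |
| Effect on day 1 only | 0.50 | 0.34 |
| Step up between days 4 and 6 | 0.00 | −0.49 |

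The last row follows from a fitted slope of (2.5 + 2 + 3)/38.5 = 0.195, and −2.5 × 0.195 = −0.49.

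**The case against.** The strongest reply is that the stated aim is to compare morning with evening PA, and that contrast has a randomised order. This stands, with two small exceptions: a 20:19 split would leave 5 × 1/39 = 0.13 day, and the different start times of the 24-hour windows (section 2.5.1) leave 0.46 day. A reader might infer that the trial's main comparison is compromised. The documents do not support that.

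A reader might also infer that all shared drift over the nine days is credited to PA. That is too strong. The second no-PA day falls after the first PA block, so under linear drift only 31% enters, and a step between days 4 and 6 leaves the unadjusted contrast unbiased.

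The drift is assumed. At the top of the range used here, the day-1-to-day-9 change of 0.8 SD is already about as large as the planned effect; larger drifts give larger error rates but need a trend bigger than that effect. Diet-related drift may also be partly absorbed by the diet covariate, though not in the ANOVA or Friedman test. Visible readings apply only to participants after the sensor change.

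Finally, a condensed article may leave time terms to a fuller plan. That carries some weight. However, the article does list its covariates, the usual crossover period term would not help, and no analysis plan can randomise the position of no PA after the event.

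**Conclusion.** The point holds for the PA-versus-no-PA contrasts, for glucose and sleep, and for the three-condition test that contains them. The mechanism follows from the schedule and the listed models: 2.5 days' worth of any linear shared trend, in either direction. The size is not known. Over the assumed 0.05 to 0.10 SD per day, the false-positive rate of the three-condition test is about two to six times nominal (1.5/0.7 to 4.3/0.7). This rests on N = 36, balanced sequences, correlation 0.15 and linear drift.

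It would be tempting to say that a linear day term restores validity. It does so only for linear drift. It removes most of a smooth settling effect and about a third of a day-1-only effect, and it creates bias for a mid-schedule step. The lasting conclusion is that PA versus no PA is a non-randomised comparison and should be read as such.

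**What to change.** 1. Make morning versus evening PA the randomised confirmatory contrast, in place of the three-condition omnibus test.
2. Label all PA-versus-no-PA contrasts, for glucose and sleep, as non-randomised.
3. Report those contrasts unadjusted and, beside that, from a day-level mixed model with study day (1, 3, 4, 6, 8, 9) as a linear covariate. Call the second a sensitivity analysis. Do not fit study day as separate categories: each day is either PA or no PA for everyone, so the categories would be fully confounded with that contrast.
4. Diet is recalled on only one of the two days per condition (section 2.5.6). In the day-level glucose model, either carry the condition-level value to both days or leave diet out, and say which.

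**Cost.** No change to the schedule or data collection. The SE is about 8% larger for one timing versus no PA and 10% larger for both pooled, with no loss for morning versus evening. The stated power of 0.89 belongs to the three-condition test and would have to be restated for the two-condition contrast. Section 2.3 keeps the investigators blinded until the results are drafted, so the change can still be fixed before unblinding.

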**Methods:**

The eligibility criteria include singleton pregnancies in patients aged 18–40 years, identified as having gestational glucose intolerance [(GGI), a non-fasted, 50-g glucose challenge test, 1-hour value ≥130 mg/dl] or gestational diabetes mellitus [(GDM), by the one- or two-step procedure, at ≥24 weeks]. Participants who provide consent are randomized to first perform either morning PA (between 5 a.m. and 9 a.m., within 30 min–40 min of starting breakfast) or evening PA (between 4 p.m. and 8 p.m., within 30 min–40 min of starting dinner). All PA episodes consist of 30 min of moderate-intensity walking or stepping. Participants ultimately contribute 2 days in each of the three treatment conditions: morning PA, evening PA, and no PA, with one washout day between treatment conditions. Timestamped glucose measurements are obtained using Dexcom G6 or G7 continuous glucose monitors (CGM). The primary analysis will be intention-to-treat; per-protocol associations will also be explored. PA adherence is assessed using ActiGraph PA monitoring devices (i.e., the CentrePoint Insight Watch, worn on the non-dominant wrist), which provide continuous timestamped estimates of movement. Participants upload photos (i.e., in real time) of all foods and beverages consumed throughout the study period, and the timestamps of these photos are used to identify postprandial periods. One 24-hour dietary recall, aided by photo uploads, is also completed for each treatment condition.

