#### Study e-surveys

2.5.5

Study data are collected and managed using the REDCap electronic data capture tools hosted at the University of Tennessee Health Science Center. Each morning, participants receive a text message with a link to a *Daily Sleep Survey* to complete upon waking. The *Daily Sleep Survey* includes a modified version of the Pittsburgh Sleep Quality Index [PSQI (41)] with questions pertaining specifically to sleep the night before (as opposed to usual sleep habits during the past month, as in the original PSQI). The *Daily Sleep Survey* assesses the time they went to bed the night before, the time they fell asleep, the time they woke up for the day, the number of times they woke up during the night (e.g., to go to the bathroom), the quality of their sleep the night before (i.e., very poor, poor, fair, good, or very good), use of medication to help with sleep, the presence of a bed partner, whether they had trouble sleeping, and the reason they had trouble sleeping (i.e., could not get to sleep within 30 min, had to get up to use the bathroom, could not breathe comfortable, coughed or snored loudly, felt too cold, felt too hot, had pain, other—please describe). The *Daily Sleep Survey* also assesses (i.e., for the day before), napping, whether or not they completed their assigned PA, periods when the CentrePoint Insight Watch was removed, and whether they experienced an injury or accident. *A priori* metrics of interest included the duration (length in hours and minutes) of sleep, sleep efficiency (percentage of time spent asleep while in bed), and sleep quality (i.e., very poor, poor, fair, good, or very good).

Participants additionally complete a *Daily Meal Times Survey* each evening to collect data on the exact times they started breakfast, lunch, and dinner that day.

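### The sleep models adjust survey-reported sleep outcomes for sleep duration and night wakings, which are an outcome and a post-treatment measure of the same night, so the total effect of condition on sleep is not estimated

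*Protocol article*

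**What the plan says.** The Background lists sleep among the secondary outcomes: "Secondary outcomes include mood during and sleep following bouts of PA".

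Section 2.5.5 (Study e-surveys) describes a survey completed each morning about the night just past. Three measures are named in advance. The first two appear in this passage: "metrics of interest included the duration (length in hours and minutes) of sleep, sleep efficiency (percentage of time spent asleep while in bed"). The third is a five-level rating of quality. The same survey records "the number of times they woke up during the night (e.g., to go to the bathroom").

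Section 2.8 (Statistical analyses) then sets the survey measures side by side for all three conditions by means of "linear mixed-effects models adjust for GGI or GDM status, sleep duration, number of waking episodes, and PA". Nothing restricts any of these covariates to particular sleep outcomes. In the preceding sentence the activity covariate of the glucose models is defined as background activity from daily living. In the sleep sentence the term is plain 'PA', with no definition.

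**The concern.** A secondary question of the trial is whether condition changes sleep. To answer it, the model must leave the sleep response free to differ between conditions. The stated model instead holds two parts of that response fixed. One of them, duration, is itself a named outcome. The other, the number of wakings, is reported for the same night and comes after the assigned activity.

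If the sentence is followed literally, one of the three a priori survey metrics has a guaranteed null result, and the other two are reported for a different quantity from the one the reader expects. The Background itself suggests that activity timing may act on metabolism partly through sleep. A null produced by the covariate list could be read as evidence against that.

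**Working it through.** **The plan's own figure.** The article gives no effect size or power for sleep. Its one computed design figure concerns glucose. f = √(0.15 × 3 / (1 − 0.15)) = 0.728, stated as 0.73. With N = 36, df 2 and 70, alpha .007 and noncentrality 0.73² × 36 = 19.2, power is 0.888 (0.885 with the unrounded f), against the stated 0.89. It reproduces and does not bear on this point.

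**Duration as outcome.** Let D be a participant's sleep duration on a night. The stated model has the form

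D = participant + condition effect + γ·D + other terms + error.

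It is fitted perfectly by γ = 1 with every other term and the error at zero. The condition effect is 0 whatever the truth. This is algebra and needs no assumption.

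**Efficiency as outcome.** From section 2.5.5, E = 100 × D / T, with T the time in bed. At fixed D, conditions can differ in E only through T. Any gain in efficiency that comes from sleeping longer is removed. How much remains depends on how condition, D and T are related, which the article does not say.

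**Quality as outcome.** In a linear model,

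total effect = direct effect + (effect on duration × slope of quality on duration) + (effect on wakings × slope of quality on wakings).

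Adjusting for both variables leaves the first term only. Even that reading requires that nothing unmeasured drives both the covariates and quality on the same night. Pain or feeling too hot, both listed in the survey as reasons for poor sleep, could do so.

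**Illustration (all sleep inputs are assumptions).** 400 simulated data sets, 36 participants, three conditions, two days each, within-participant linear model. Assumed effects against no PA:
- Duration: +0.25 h (morning) and +0.50 h (evening).
- Wakings: −0.2 and −0.4.
- Quality: +0.4 per hour slept, −0.2 per waking, direct effects 0.1 and 0.2.
- Time in bed: rises 0.3 h per hour slept, with no separate condition effect.

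The assumed total effect of evening PA on quality is 0.2 + 0.5 × 0.4 + 0.4 × 0.2 = 0.48.

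| Outcome, contrast | No covariates | Covariates in model | Estimate with covariates |
|---|---|---|---|
| Duration (h), evening vs none | 0.50 | duration | 0 exactly |
| Efficiency (points), evening vs none | 4.5 | duration, wakings, total PA | about 0.0 |
| Quality, evening vs none | 0.48 | duration, wakings, total PA | 0.20 |
| Quality, evening vs morning | 0.24 | duration, wakings, total PA | 0.10 |
| Quality, evening vs none | 0.48 | total PA only | 0.48 (SD of estimate 0.12 → 0.15) |
| Quality, evening vs morning | 0.24 | total PA only | 0.24 |

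A separate simulation with other assumptions (+20 min of sleep and 0.3 fewer wakings in one condition) gave 4.1 → 2.0 points for efficiency. The gap between about 0.0 and 2.0 shows that the loss for efficiency cannot be fixed from the article.

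**The PA covariate.** Participants are "randomized in SAS to either morning PA followed by evening PA or evening PA followed by morning PA", and "All PA episodes consist of 30 min of moderate-intensity walking or stepping". Assigned volume is thus equal in the two active conditions, and adjusting for volume does not remove the contrast between them. The unchanged PA-only rows also rest on the simulation's assumption that background activity neither differs by condition nor affects sleep.

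**The case against.** Several points can fairly be made for the plan.

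- *A condensed article pools covariates for several metrics, and no analyst would regress duration on itself.* This is plausible, and the degenerate fit would be noticed. But the list is stated without limits, whereas the next sentence, on mood, makes its covariates optional. On the charitable reading, efficiency and quality are still adjusted for duration and wakings, so the defect is reduced and not removed.
- *Detail belongs in the analysis plan.* That would answer an omission. Here the covariates are affirmatively stated.
- *Holding duration fixed might be of interest.* It might, as a mediation question, but the article does not present it as one.

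Some stronger readings are tempting, and the article does not support them:

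- *That the model adjusts away the treatment through 'PA'.* The term is undefined in that sentence and may mean background activity. Even as total activity it would mainly cost precision for PA versus no PA, and it would not remove morning versus evening at 30 min in both.
- *That wakings are a component of the outcomes.* They enter no formula for duration, efficiency or quality; they are a possible mediator.
- *That the sleep question cannot be answered at all.* Section 2.5.4 adds device-assessed sleep metrics as secondary outcomes, and section 2.8 does not tie them to this covariate list.
- *That the bias is always toward no effect.* Conditioning on post-treatment variables can move an estimate either way.

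**Conclusion.** The covariate list is wrong as written. For survey-reported duration the condition effect is zero by identity, with no assumption needed. For efficiency and quality the model does not estimate the total effect of condition; at most it estimates what does not pass through duration and wakings. The amount lost is not determined by the article. Under assumed effects it ranged from half to nearly all of the efficiency effect and was a little over half of the quality effect (0.48 to 0.20), and these figures are illustrations only.

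The point is confined to the modified PSQI metrics, a secondary outcome. The glucose comparisons, the .007 level and the sample size of 36 (39 randomized) are untouched. 'PA' needs a definition, which is a lesser matter of wording.

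**What to change.** 1. Remove sleep duration and the number of wakings from the main sleep models. Adjustment for GGI or GDM status can stay, since it is a baseline stratification factor.
2. Compare duration and wakings across conditions as outcomes in their own right.
3. If adjustment for either is wanted for efficiency or quality, present it as a labelled mediation or sensitivity analysis, and never use duration as a covariate for itself.
4. State that 'PA' in the sleep models means background activity excluding the assigned bout, as in the glucose models.

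The cost is a few sentences of analysis text, best settled before unblinding. All the survey items are already collected, so no new data are needed and the sample size does not change.
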